Eligible patients are invited for a diagnostic interview — consisting of the Structured Clinical Interview for DSM-IV Axis II Personality Disorders (SCID-II) — to determine the presence of Axis II disorders and other inclusion and exclusion criteria. Beforehand patients receive the AQ and the pre-screener of the SCID-II. During the SCID-II interview all cluster C personality disorders are fully investigated. All confirmatively answered and all unanswered questions on the pre-screener will also be assessed with the SCID-II interview. If the personality trait is confirmed and the amount of confirmed traits pertaining to a certain personality disorder exceeds three, all traits pertaining to that personality disorder will be assessed with the SCID-II interview. Besides scores on the pre-screener, clinical judgement can also be a reason to fully examine a certain personality disorder. In addition to SCID-II, the Mini-International Neuropsychiatric Interview (MINI), section social anxiety, is also administered. The MINI interview is part of the intake procedure of both anxiety departments of PsyQ in addition to a general clinical interview. Some of the patients entering this study will have recently signed up for treatment and will have completed this procedure, but referral by other departments or during ongoing treatment is also possible. It was therefore decided to add the SAD section of the MINI to ensure that patients included meet the inclusion criteria of both SAD and APD.

During the examination, patients will receive additional verbal and extensive written information about the study with respect to both treatment conditions and consequences of participating. After conclusion of the SCID-II administration, patients will be either informed directly or receive a follow-up appointment to discuss the findings of the interview. Patients will have 2 weeks to consider participation, after which they will be contacted by a research assistant. Written informed consent will be obtained from patients who are willing to participate, and they will be asked to fill in the baseline assessment comprising different self-report questionnaires. To be able to assess the frequency and severity of manifestations of APD, a semi-structured interview was developed: the AVPDSI. The AVPDSI interview is administered by phone by a trained psychologist or a trained master student in clinical psychology who fulfils a traineeship at the PsyQ anxiety department.

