After a final file check of inclusion and exclusion criteria based on the patient file and after all baseline measures are completed, a research assistant will randomize the patients to the GCBT or GST condition using a computer-generated list (https://www.random.org/lists/). Patients will be randomized in pairs or multiples of pairs. In case of uneven dropout from treatments, a weighted randomization will be done to prevent one of the groups from becoming too small. For both locations this will be done separately.

The main researchers and other outcome adjudicators are blind to group assignment to protect integrity of data collection and analysis. Because it is impossible for a therapist to offer and for a patient to receive therapy without being aware of the techniques they are using or receiving, therapists and patients are not blind. Finally, because data collectors are also employed as therapists in the anxiety departments of the participating sites, they are able to access patient records. Therefore, data collection of clinician-administered measures cannot be blinded. To reduce the risk of biased data collection, therapists involved in delivering either the GCBT or GST are not involved in data collection.

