### Instruments

The measures described below will be administered on different measurement occasions. At all time points self-report measures will be conducted online, except for the AQ and pre-screener of the SCID-II used in the inclusion and exclusion procedure (see inclusion procedure above). On request, participants can complete the self-report measures on paper.

The administration of the SCID-II and the MINI during the intake phase will be conducted face to face. At the last assessment (T5) patients can choose between a face-to-face or telephone administration of the SCID-II, APD section and the MINI, SAD section, according to their preference. For practical reasons, all AVPDSI assessments are administered by phone. Research supports the validity of structured telephone interviews for data collection from primary care patients [35]. See Fig. 1 for the exact measurements per occasion. To ensure privacy of participants and safe data storage, data will be entered in a data file anonymously; participants will be given a unique number, and only the research assistant will be able to link the number with the name of the patient. Data will be stored on a laptop used only for research purposes, and a salted and encrypted file server which has been advised by an independent tech consultant.

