### Primary outcome measures

The primary outcome measure for severity of social anxiety is the *self-report version of the Liebowitz Social Anxiety Scale (LSAS-SR).* The objective of the LSAS [36] is to assess the range of social interaction and performance in situations which patients with SAD may fear. The scale contains two parts: one part measures the level of anxiety, and the other part measures the level of avoidance. It consists of 24 items, 13 relating to performance anxiety and 11 concerning anxiety in social situations [37]. The LSAS was originally developed as a clinician-administered semi-structured interview. The LSAS self-report version has comparably good psychometric properties (convergent and discriminant validity, internal consistency, test-retest reliability, criterion validity), high correlation with the clinician-administered version and sensitivity to treatment change. Furthermore, the self-report version is easier to administer and is less time-consuming for both patient and clinician [38–40]. The LSAS-SR will be administered at all time points, i.e. at the start, halfway and at the end of the treatment period and during follow-up at 3, 6 and 12 months after study treatment (see Fig. 1).

The primary outcome measure for severity of APD is *the clinician-administered Avoidant Personality Disorder Severity Index (AVPDSI).* The AVPDSI is a semi-structured interview developed specifically for this study to assess the frequency and severity of manifestations of APD, as defined in the DSM-IV/5, during the last month. The purpose of this instrument is to yield a quantitative index of the current severity of APD manifestations, in terms of both avoidance and fear. The AVPDSI is modelled after the Borderline Personality Disorder Severity Index (BPDSI), which was originally developed by Weaver and Clum [41] and further developed and validated in Dutch by Arntz et al. [42] and Giesen-Bloo et al. [43]. The information gathered by the AVPDSI in the context of the RCT will also be used in a larger study in which the psychometric properties of the interview will be assessed. To ensure quality of data collection of this newly developed instrument, a training protocol will be developed and all measurements will be audiotaped. A random selection of tapes will be listened to in order to assess interrater reliability. This semi-structured interview will be conducted before the start of treatment and at 3 and 12 months follow-up (see Fig. 1).

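### Interviewers' access to patient records does not show that the AVPDSI, a telephone-administered and audiotaped primary outcome, is impossible to mask; the plan should mask the post-randomization ratings as far as it can

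*Protocol article*

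**What the plan says.** Blinding is set out in the protocol article under Inclusion and exclusion procedure and randomization. One paragraph makes these statements:

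- "The main researchers and other outcome adjudicators are blind to group assignment to protect integrity of data collection and analysis".
- Therapists and patients cannot be blind to the treatment.
- On the interviewers: "because data collectors are also employed as therapists in the anxiety departments of the participating sites, they are able to access patient records". From this the article concludes that "data collection of clinician-administered measures cannot be blinded".
- As a safeguard, "therapists involved in delivering either the GCBT or GST are not involved in data collection".

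The AVPDSI is one of two primary outcomes and the only primary outcome for avoidant personality disorder (Primary outcome measures). It is a new semi-structured interview whose psychometric properties are still to be studied. On how it is administered, the article says:

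- Mode: "all AVPDSI assessments are administered by phone" (Instruments).
- Interviewers: "The AVPDSI interview is administered by phone by a trained psychologist or a trained master student"; the student is on a traineeship in the PsyQ anxiety department (Inclusion and exclusion procedure and randomization).
- Recording: "all measurements will be audiotaped", and a random selection of tapes, of unstated size, is used for interrater reliability (Primary outcome measures).
- Timing: before treatment and at 3 and 12 months follow-up. Randomization comes only after all baseline measures are complete.

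The APD section of the SCID-II and the SAD section of the MINI are repeated at T5, face to face or by telephone as the patient prefers.

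**The concern.** The stated reason does not carry the conclusion. Being able to open a file is different from having opened it, and a trial can forbid or avoid opening it. The article treats a matter of procedure as an impossibility and therefore plans no masking, although a telephone interview that is always recorded is comparatively easy to mask.

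The AVPDSI calls for rater judgement. If interviewers know the arm, their scores can drift apart between arms, and the analysis cannot separate that drift from a treatment effect. The article itself recognises a risk of biased data collection. The limitations in its Discussion do not mention unmasked rating.

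The paragraph is also unclear about roles. It speaks of blind outcome adjudicators and of data collectors who cannot be blinded, and describes no separate task for the former. A reader could take the AVPDSI to be rated blind.

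**Working it through.** **1. Does the inference hold?** The premise is that collectors can reach the records. The conclusion is that masking cannot be done. The article's own arrangements leave room for masking:

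| Feature | Where stated | What it allows |
|---|---|---|
| Every AVPDSI by telephone | Instruments | The interviewer need not be at the patient's site |
| Every AVPDSI audiotaped | Primary outcome measures | A second rater can score without the file |
| Random selection of tapes listened to | Primary outcome measures | Some second listening is already planned |
| Two sites | Design | Interviewers from the other site are conceivable; feasibility is not documented |

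The conclusion does not follow from the premise.

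**2. Which ratings are exposed?** The baseline AVPDSI precedes allocation and cannot be influenced by it. What remains is the AVPDSI at 3 and 12 months, which is all of its post-randomization data, and the SCID-II and MINI at T5. The Statistical analysis section specifies a remission analysis for APD only.

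**3. The plan's own figure.** Population/sample size gives d = 0.5, 80% power, two-sided alpha 0.05 and 64 per group (128 in total). The two-sample t-test needs 63.77 per group, rounded up to 64, with power 0.801. The normal approximation gives 63 per group, and power 0.807 at 64. The stated figure reproduces, and nothing in this point changes it.

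**4. What a rating shift would do (illustration).** Let b be an arm-related shift in AVPDSI scores, in SD units. The article gives no value, so 0.1 to 0.3 is an assumed range. At 64 per arm the standard error of the difference is √(2/64) SD, so the shift in the test statistic is b/√(2/64) = b·√32 = 5.657b.

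With no true difference, the false-positive rate is Φ(5.657b − 1.96) + Φ(−5.657b − 1.96). With a true difference of 0.5 SD and a shift against it, power is about Φ(5.657(0.5 − b) − 1.96).

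| b (SD) | 5.657b | False-positive rate | Power if true d = 0.5 and shift runs against it |
|---|---|---|---|
| 0 | 0 | 5.0% | 80.7% |
| 0.1 | 0.566 | 8.7% | 61.9% |
| 0.2 | 1.131 | 20.5% | 39.6% |
| 0.3 | 1.697 | 39.6% | 20.4% |

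A shift of 0.2 SD is 0.2/0.5 = 40% of the difference the trial is designed to detect.

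**5. What masked scoring would cost.** Scoring every post-randomization AVPDSI tape means up to 128 × 2 = 256 ratings at full retention (128 × 3 = 384 with baseline), less those already planned. Re-rating only the planned sample adds no ratings if those tapes are scored anyway for reliability.

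**The case against.** The article is open about unblinded collection, gives a reason, and states a safeguard: those delivering the trial treatments do not collect data. It also plans interviewer training for the AVPDSI. It shows that interviewers may reach the records, not that they know the arm. Patients are unblinded in any case, so no arrangement on the rater's side can remove bias from their answers. A condensed article may also leave the masking of tape raters to the full protocol.

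Much of this stands. The safeguard is real, though partial, because the remaining interviewers still work in the same departments. The size and direction of any shift are unknown. The table assumes a uniform shift, full retention and a comparison at one time point, whereas the plan is a repeated-measures multilevel analysis. But the article does not merely leave masking to another document. It declares masking impossible on a reason that does not show this.

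Some stronger readings are tempting, and the article does not support them:

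- **That all AVPDSI ratings could be masked at no extra staffing.** Only a random selection of tapes is to be listened to, so scoring all of them is added work.
- **That the two blinding statements flatly contradict each other.** Adjudicators and data collectors may be different people. The roles need clarifying; an error is not established.
- **That student interviewers lack access to records.** They are trainees in the same kind of department, and nothing says they have no access.
- **That calling across sites is readily available.** The article does not address its feasibility.
- **That the T5 SCID-II and MINI could be re-rated from tape.** The taping statement concerns the AVPDSI.

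**Conclusion.** The point holds in this limited form: record access does not justify the statement that masking is impossible, and following the plan as written leaves avoidable rater bias in the 3- and 12-month AVPDSI and in the T5 diagnostic interviews. The baseline interview is not affected, and excluding trial therapists from data collection already lowers the risk.

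The size cannot be derived from the article. Under an assumed shift of 0.1, 0.2 or 0.3 SD at 64 per arm, the false-positive rate would be about 9%, 20% or 40%. This shows how sensitive the AVPDSI comparison is; it does not estimate the bias to be expected. The change should be made because it is cheap and protects a primary outcome. It does not affect the sample size.

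**What to change.** Replace the statement that blinding is impossible with a rule for all post-randomization clinician-administered interviews:

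1. Interviewers do not open the records of patients they interview. Where feasible, they come from the other site.
2. At the start of each interview, the patient is asked not to name the treatment received.
3. Any unmasking is logged, with patient and time point.
4. The random sample of AVPDSI tapes already planned is re-rated by raters unaware of arm. Live and masked scores are then compared by arm: a live-minus-masked difference that differs between arms points to a rating shift. Because the article does not give the sampling fraction, the precision of this comparison cannot be stated here.
5. The article says who the blind outcome adjudicators are and how they differ from the data collectors.
6. Any rating that remains unmasked is listed as a limitation.

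The cost is a procedure note, some scheduling and a log; the interviews and tapes are those already planned. Recruitment was still under way at publication (Trial status), so later interviews can follow the rule and earlier tapes can be included in the masked sample. The change could leave a mix of ratings made before and after the rule, so the date it takes effect should be recorded.

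Masking will be imperfect. Patients may disclose their arm, and a tape rater scores answers drawn out by the live interviewer. Bias is reduced, not removed.

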### Interventions

Different guidelines recommend CBT for treatment of SAD [28–30]. CBT is seen as the gold standard for SAD with respect to non-pharmacological treatment, and gains achieved with CBT seem to persist longer than those achieved with pharmacotherapy [29]. Guidelines differ with respect to the advised treatment format (individual or group therapy). The Canadian guidelines do not express any preference, NICE guidelines advise individual CBT and Dutch guidelines recommend group CBT [28–30]. None of these guidelines advises on the treatment of SAD and comorbid APD. With respect to APD, guidelines are scarce. Dutch multidisciplinary guidelines recommend group behavioral treatment for patients with APD. They specify that in case of comorbidity of SAD and APD, CBT is seen as an adequate treatment option, although prolonged treatment is necessary to realize comparable favourable outcomes as for SAD only [13].

GCBT is a regular treatment option and fits neatly in the health care program offered at the RCT participating departments of anxiety disorders. GST will be a new treatment, but will be performed by skilled and experienced therapists. Both treatments were piloted in advance to enable therapists to become acquainted with the treatment protocol and the semi-open group format. In the ST condition therapists had no former experience with ST in a group format; therefore, this treatment modality was permitted an 8 months longer pilot period. In The Hague the pilot period for GST was 18 months and for GCBT 10 months. In Rotterdam the pilot period for GST took 32 months and for GCBT 24 months, this was due to a major reorganisation. 

For patients of both GST and GCBT, treatment comprises of 30 weekly group sessions of 90 minutes, preceded by 2 introductory individual sessions of 45 minutes. In addition to the group treatment, limited individual time with the therapist is permitted with a maximum of 180 minutes. Individual contact can take place in person or by phone or e-mail and can be initiated by either patient or therapist, for instance if urgent personal matters come up or if the therapist fears dropout and wants to discuss possible obstacles for the patient. Sessions will be audiotaped to assess protocol adherence. For both GST and GCBT, customized rating forms will be developed and a random selection of tapes will be listened to in order to evaluate to what extent therapists adhere to the protocol.

### Group schema therapy (GST)

GST is a recently developed treatment for personality disorders. GST is shorter, more directive, confrontational and integrative — using experiential, cognitive and behavioral techniques, addressing childhood and present — than traditional psychodynamic psychotherapies for personality disorders. Schemas can be described as psychological constructs that include beliefs that we have about ourselves, the world and other people, which result from interactions of innate temperament and early environmental factors, notably trauma and unmet core childhood needs. When maladaptive schemas are triggered, specific states occur, as the result of the combination of activated schema(s) and type of coping, that can be described as schema modes. Schema modes are central in GST. Schema modes often had an adaptive role in childhood (e.g. in terms of survival in an adverse situation), but become maladaptive and limiting in adulthood. GST aims at reducing the use of dysfunctional coping modes, healing the maladaptive child modes, banishing the internalized parent modes and strengthening the adaptive modes (healthy adult mode and happy child mode). The ultimate goal of GST is to enable patients to get their emotional needs met, including gaining autonomy and forming healthy social relationships. In GST the group is used as an analogue for the family of origin with the other group members as ’siblings’ and the therapists as ’parents’. Group processes can be used to create corrective emotional experiences and to reduce maladaptive coping modes [24].

For this study, a 30-session treatment protocol of 90-minute weekly sessions over 9 months was developed. The treatment protocol is naturalistic in the sense that, apart from the framework directing treatment focus throughout sessions, therapists do not have a session-to session detailed treatment manual. The structure of the group will be semi-open, and every 10 weeks new patients can enter an ongoing group. Before a patient enters the group, two individual meetings will be planned to provide some information about the content and the process of GST, to discuss briefly the results of the Schema Mode Inventory (SMI) and to formulate a case conceptualization in schema mode terms in collaboration with the patient.

Participants are encouraged to engage in homework between sessions to gain corrective experiences in line with individual needs. Thus, homework does not focus on exposure to social situations that are feared, but on finding ways to better meet one’s needs. Each course will be provided by two experienced therapists who received formal GST training by [name]. They will receive monthly supervision (1.5–2 hours) by [name] using Skype.

### Group cognitive behavioral therapy (GCBT)

GCBT will follow a prolonged version of the well-investigated protocol of Heimberg and colleagues of group therapy for SAD [31–33] in combination with some new insights in the working mechanisms of exposure in vivo [34]. GCBT will mainly consist of simulated exposures to feared situations in-session, cognitive restucturing and in vivo exposure to feared social situations between sessions. Just as in the GST, the format of the group will be semi-open, allowing new patients to enter the group every 10 weeks, and the group treatment of 30 weekly sessions is preceded by 2 individual sessions.

The individual sessions are aimed at facilitating the start of the group treatment. During these sessions information about the content of the therapy is provided and an individual case conceptualization is drawn. Emphasis will be placed on the role of avoidance and safety-seeking behaviors in the maintenance of SAD. The basics of cognitive restructuring will be presented, and patients will be asked to write down a list of feared situations which will be placed in a hierarchical sequence. Social anxiety will be considered as a learned response to social situations incorporating interactive physiological, behavioral and cognitive features. Social anxiety disordered patients supposedly fear most social situations because of their expectancies to be humiliated or rejected by others or confrontations with their own supposed social inadequacies and failure. The main therapeutic target in GCBT is the disconfirmation of these dysfunctional expectancies. To a small extent one strives for these disconfirmations using traditional cognitive procedures such as identification, intellectual challenging and (possibly) correcting of dysfunctional opinions. By far the largest part of the CBT procedure of disconfirming such expectancies exists of exposure in vivo. Since the understanding of the working mechanisms of exposure in vivo has changed in recent years, the main target of exposure in vivo is no longer habituation of the fear response. Nowadays it is believed that exposure in vivo sets off a process of inhibition in which the association of the conditioned stimulus (CS) (social situations) and the feared unconditioned stimulus (US) (humiliation) is inhibited by the forming of new associations around the CS, of which the association with ‘no-US’ (no rejection) is probably the most important [34]. During group sessions and for homework, patients expose themselves deliberately to the social situations they fear in order to let new non-anxious associations form and to experience in particular that the negative consequences they expected in advance did not become true in reality. Noticing the differences between the expected and the actual outcomes of these confrontations is an important subject for therapeutic discussion after exposure. Therefore, the GCBT protocol is a mix of the well-proven approach of Heimberg and some new insights in the mechanisms of exposure in vivo.

Most group sessions will focus mainly on performance-based gradual and systematic exposure with elimination of the accompanying safety behaviors. Self-exposure to situations that resemble the exposure practiced in-session is prescribed as homework to further promote correction of negative expectancies. GCBT is highly structured, with each session following the same agenda including discussing homework assignments, in-session performance-based exposure and assigning new homework. The group is used to provide an immediate exposure setting while it offers the possibility of vicarious learning from other group members at the same time. The group is, however, mainly disorder-specific in a sense that the primary goal is reduction of social anxiety symptoms. In contrast to GST group processes, childhood experiences and experiential exercises will not be used to promote symptom reduction. Each course will be provided by two experienced cognitive behavioral therapists who have been trained in the specific GCBT protocol. During the trial the therapists will receive supervision every 2 weeks (0.45 to 1 hour) by a licensed CBT supervisor.

